### Strategies to improve adherence to interventions {11c}

The acupuncture treatment scheme is safe and can be adjusted according to the needs of patients, so the compliance rate of the protocol is very high, and the whole process of acupuncture treatment will be supervised by professional acupuncturists in our center.

### Relevant concomitant care permitted or prohibited during the trial {11d}

During the trial, other drugs affecting gastrointestinal function can be used according to the doctor’s advice. If used, detailed records are required. If patients have intolerable postoperative pain or other postoperative symptoms, conventional drugs can be used for emergency treatment.

### Provisions for post-trial care {30}

After waiting for the end of the experiment, the control group will receive 4 acupuncture treatments free of charge. If the subject is injured by acupuncture during the study period, acupuncture should be stopped immediately, symptomatic treatment should be given free of charge, and psychological counseling should be given to the patient at the same time. If the injury is serious, invite relevant experts for treatment and compensate for medical expenses.

### Outcomes {12}

#### Primary outcome

Time of first postoperative flatus is the study’s primary outcome and is measured as the time period starting from the patient’s return to ward after the laparoscopy procedure till the first passage of flatus. It is obtained through the assistance of family members and caregivers, via inquiry and record of patient’s status.

#### Secondary outcomes

Secondary outcomes include the time of first postoperative defecation, time of first fluid intake, and time of first ambulation, which are obtained through the assistance of family members and caregivers, via inquiry and records of patient’s status. Other secondary outcome measures such as gastrointestinal reaction score (postoperative pains, distention, nausea, vomiting), acupuncture sensation evaluation scale, laboratory test, postoperative hospital stay, quality of life, readmission rate, and other postoperative complications (fever, pneumonia, wound infection, bleeding, etc.) are assessed and evaluated by our investigators. The first postoperative evaluation of all patients was performed 12–24 h after operation to ensure that the patients were awake.

For gastrointestinal reaction score, postoperative pain will be evaluated regularly at three times a day using the visual analog scale (VAS), and the three scores will be averaged and tabulated with dosage and frequency of patient-controlled analgesia (PCA) and analgesic medication used. The extent of distention is recorded using the Likert scale [17], postoperatively from day 1 to 4. The extent of nausea is recorded using the VAS, postoperative from day 1 to 4. Vomiting will be counted daily.

For Acupuncture Sensation Evaluation Scale, acupuncture sensations are assessed after every acupuncture treatment session through inquiring about patient’s sensations.

For laboratory test, venous blood will also be collected on the day prior to operation, as well as the first and third day after the laparoscopy, to assess the safety of acupuncture base on blood examinations and biochemical indicators.

Postoperative hospital stay is measured from the day of the laparoscopy procedure till the day of discharge.

Quality of life is assessed through the Quality of Life Questionnaire (QLQ-c30), provided to patients prior to operation and 1 month after the operation [18].

For readmission rate, evaluate the readmission of patients 1 month after the operation, record the reasons for readmission in detail, and finally calculate and analyze.

Adverse events include postoperative complications and adverse acupuncture events. Postoperative complications are recorded and evaluated using the Clavien Dindo Classification [19]. Adverse acupuncture events including subcutaneous hematoma, continuous acupuncture afterfeeling, and needle stagnation will be recorded by the assessor.

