**Fig. 1 Fig1:**
[figure not shown]
Flowchart of the study design

The purpose of this study is to design a high-quality randomized controlled trial and realize the complete randomization of participants, and the evaluators and data analysts are blinded, so as to provide reliable data for the recovery of gastrointestinal function of colorectal cancer after acupuncture treatment. However, the framework of this trial is not perfect. First, this study failed to establish false acupuncture, and the comforting effect of acupuncture cannot be ruled out. Second, the included cases are completely random without too many restrictions, but the clinical situation of patients is complex, and the tumor stage, operation mode, and TCM syndrome type may be related to the speed of postoperative gastrointestinal function recovery. It is better to carry out stratified observation. Third, both patients received perioperative care guided by eras, which achieved the ceiling effect, and the acupuncture effect may not be obvious. Fourth, the patients knew the grouping situation and were not blinded.

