#### Implementation {16c}

After ensuring patients fulfill inclusion criteria and informed consent forms are obtained from them, the envelopes are opened by the acupuncturist and acupuncture treatment is carried out (the acupuncturist is excluded from assessment and statistical analytic process as blinding of the acupuncturist cannot be achieved). The study group will be revealed at the same time to both the patient and researcher.

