### Assignment of interventions: blinding

#### Who will be blinded {17a}

Throughout the study, the statisticians and evaluators are blinded, so that independent assessments and statistical analysis can be carried out. The subjects in the control group could not be blinded due to their particularity. Acupuncturists were not blinded in this study.

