### Oversight and monitoring

#### Composition of the coordinating center and trial steering committee {5d}

This is a single-center study designed in Dong Fang Hospital of Beijing University of traditional Chinese medicine and implemented and coordinated in Cancer Hospital of Chinese Academy of Medical Sciences.

Daily support for the trial was provided by:

Main responsible person: responsible for supervising the trial and the medical responsibility of patients.

Data manager: organize data capture and protect quality and data.

Study coordinator: trial registration, informing patients, coordinating study visits, and annual safety report.

Research surgeons: recruit patients, evaluate their postoperative recovery, and ensure follow-up in accordance with the agreement.

The study team meets biweekly. There is no trial steering committee or stakeholder and public involvement group.

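### The assessor, declared blinded, is also assigned to record needling events that only the acupuncture arm can have

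*Protocol article*

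**What the plan says.** On blinding, Who will be blinded {17a} states: "Throughout the study, the statisticians and evaluators are blinded, so that independent assessments and statistical analysis can be carried out". The text under Fig. 1 in Trial design {8} repeats that evaluators and analysts are blinded, and the Discussion cites it when it calls the trial's reliability high.

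On who records what, Secondary outcomes states: "Adverse acupuncture events including subcutaneous hematoma, continuous acupuncture afterfeeling, and needle stagnation will be recorded by the assessor". It also says of the sensation scale that "acupuncture sensations are assessed after every acupuncture treatment session through inquiring about patient’s sensations". The same section lists that scale with the gastrointestinal reaction score, quality of life and complications as work of the trial's investigators, and does not say which of them are blinded.

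On who knows the allocation, Implementation {16c} has the acupuncturist open the envelope and explains that "the acupuncturist is excluded from assessment and statistical analytic process as blinding of the acupuncturist cannot be achieved". It adds: "The study group will be revealed at the same time to both the patient and researcher". That researcher is not identified.

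On the primary outcome, time to first flatus, the article says: "It is obtained through the assistance of family members and caregivers", by inquiry and by recording the patient's status. The text under Fig. 1 discloses: "Fourth, the patients knew the grouping situation and were not blinded".

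**The concern.** The trial has no sham, so blinding of outcome evaluators is its main stated protection against observer bias. That protection works only if the evaluator meets nothing that identifies the arm. A record of what happened when needles were in place, or of what the patient felt during needling, identifies it at once.

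At stake are the comparative secondary outcomes that involve an observer's judgement or questioning: distension, nausea and the grading of complications. An observer who knows the arm may probe or grade differently, and the report would still describe these outcomes as blindly evaluated. A reader of the Discussion could also assume that evaluator blinding covers the primary outcome.

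**Working it through.** No arithmetic applies and the plan gives no figure to reproduce. The check sets the provisions side by side.

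1. **Can the control arm produce the recorded events?** Table 2 shows no intervention for controls, and the Control group section gives them ERAS care without acupuncture. Needle stagnation and after-feeling from needling therefore cannot occur there. Subcutaneous hematoma is less decisive, because both arms have venous blood drawn. The argument needs only the other two.

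2. **Who records them?** Secondary outcomes names the assessor. The acupuncturist would be the natural alternative, but Implementation {16c} excludes the acupuncturist from assessment. No other unblinded recorder is named.

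3. **Is the assessor the person declared blinded?** Who will be blinded {17a} covers evaluators without exception and for the whole study. The article does not define an assessor as someone distinct from an evaluator. Read together, these provisions have a blinded person record an event that reveals the arm.

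4. **Does the sensation scale add to this?** It is asked after every session, and sessions run daily for 4 days in the acupuncture arm. Secondary outcomes gives it to investigators in general, in one list with the gastrointestinal score and complications. The text neither says that one person does both tasks nor prevents it.

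5. **Is there another route?** The group is revealed to an unspecified researcher when the envelope is opened. Nothing says that this researcher is an evaluator, and nothing says otherwise. Procedure for unblinding {17b} allows unblinding only in emergencies, so routine disclosure to an evaluator would also conflict with that section.

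6. **How many patients?** Under steps 1 to 3, every patient with an after-feeling or stagnation entry is affected; the article gives no expected rate. Under step 4, if the outcome evaluator also asks the sensation scale, all of the planned 80 acupuncture patients are affected, and controls are identified by having no scale. The document does not settle where between these the trial lies.

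7. **What does evaluator blinding do for the primary outcome?** Flatus is reported through inquiry, with help from family members and caregivers, and patients know their group. A blinded person who writes down an unblinded report does not make the report blinded. The Discussion names only rectal tubes as a source of inaccuracy in flatus reporting.

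**The case against.** The strongest reply is that this is a loose word in a condensed article. Adverse event reporting and harms {22} already provides a dedicated record form for acupuncture safety, completed around each patient's treatment, and the full protocol may say who fills it in. That answers part of the concern: a form exists. But the section names no recorder and does not keep the form from evaluators, while Secondary outcomes does name a recorder, and it is the assessor. That is a conflict in what is written, not a detail left out.

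It is also fair that pain and nausea use visual analog scales, which patients ordinarily mark themselves, and that vomiting is counted. For such items the larger exposure is the patient's own knowledge of the arm, which is disclosed. Observer influence is most plausible for complication grading and for anything obtained by questioning.

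A reader might infer several stronger points that the document does not support:

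- **Allocation is known for essentially every patient from day 1.** This needs the blinded evaluator personally to ask the sensation scale, which is not stated.
- **The surgeons' two roles break the blind.** The article says: "Research surgeons: recruit patients, evaluate their postoperative recovery, and ensure follow-up in accordance with the agreement". Recruiting does not reveal allocation, since the acupuncturist opens the envelope after eligibility and consent.
- **The statistician is unblinded by the sensation data.** That depends on which variables enter the analysis file, which is not described.
- **Unblinded reporting of the primary outcome is concealed.** Patients' knowledge of their group and the role of families are both stated. That families know the arm is a reasonable inference, not a stated fact.
- **The bias can be sized from the 8 h target.** One hour of differential reporting is 1/8 = 12.5% of it, but that is division. The document gives no estimate of the bias or its direction.
- **The blinding claim is false as executed.** No conduct data are shown.

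**Conclusion.** The contradiction stands. The article declares evaluators blinded throughout and relies on this, while assigning the assessor to record events that can occur only in the acupuncture arm and excluding the one person who could record them without harm. Any such entry reveals the allocation to someone meant to score comparative outcomes blind. The missing split of staff for the sensation scale and the unidentified researcher leave further routes open, but do not show that the blind is broken by them.

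The number of patients affected and the resulting bias cannot be derived. The conclusion assumes that assessor and evaluator mean the same role, which is the natural reading because the article draws no distinction. For the primary outcome the narrower conclusion is that evaluator blinding gives little protection, and the Discussion's reliability claim should say so.

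**What to change.** - **Recording.** Have the acupuncturist complete the sensation scale and the needle-related events, using the form in Adverse event reporting and harms {22}, and keep that form from outcome evaluators. Change the recorder named in Secondary outcomes to match.
- **Implementation {16c}.** Amend the exclusion so that it covers only assessment of the comparative outcomes. Without this, the new recording rule would contradict it.
- **Who will be blinded {17a}.** State that outcome evaluators do not attend sessions, do not ask about them, and are not the researcher to whom the group is revealed.
- **Secondary outcomes.** Report the sensation scale as a measure in the acupuncture arm only.
- **Discussion.** Limit the reliability claim: evaluator blinding does not protect time to first flatus, which is obtained by inquiry from patients who know their group and from their families and caregivers.

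The cost is slightly more recording for the acupuncturist, who is already present and unblinded, plus the rewording. Treatment and sample size do not change. Trial status reports that recruitment began in October 2020 and was continuing, so the change can help only patients not yet assessed. The report should say from what date it applied.

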### Participant timeline {13}

The participant timeline is presented in Table 1.

### Sample size {14}

Our study estimates that a mean decrease of 8 h in time of first flatus after application of acupuncture to promote recovery in postoperative gastrointestinal functions is of significant value. The literature review showed the standard deviation of time of first flatus between the study group and control group to be 12.28 and 14.57, respectively. Using a unilateral test of superiority, PASS.11 software is used to compute sample size. Using *α* = 0.05, *β* = 0.1, and power = 0.9, 68 subjects are required in each group, with a total of 136 subjects needed for the study. Estimating a 20% dropout rate, a minimum recruitment of 160 subjects is required.

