### Statistical methods

#### Statistical methods for primary and secondary outcomes {20a}

Spss22.0 software was used to analyze and process the clinical observation data, in which in the descriptive statistical analysis, qualitative indicators were described by frequency table and percentage and quantitative indicators were described by mean and standard deviation. Comparison of the two groups was performed: quantitative data in line with normal distribution using the *t* test, homogeneity test of variance between groups, with 0.05 as the test level, uneven variance using Satterthwaite method for correction of *t* test, and not in line with normal distribution using Wilcoxon rank-sum test. The hypothesis test uses a two-sided test and gives the test statistics and the corresponding *p* value, with *p* ≤ 0.05 as statistically significant. All (S)AE(I)s will be summarized and recorded including the nature, date and time of onset, date of resolution, determination of seriousness, severity, action taken, outcome, and possible causality to study treatment. SAE data will be presented in a descriptive manner.

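### The sample size is described as one-sided at 0.05 while the analysis is two-sided at 0.05, and the stated 68 per group follows from the stated inputs under neither; the error is on the safe side

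*Protocol article*

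**What the plan says.** Sample size {14} in the Protocol article takes as its target "a mean decrease of 8 h in time of first flatus after application of acupuncture". From a literature review it takes "the standard deviation of time of first flatus between the study group and control group to be 12.28 and 14.57, respectively". The test is named in the sentence "Using a unilateral test of superiority, PASS.11 software is used to compute sample size". The result follows: "Using *α* = 0.05, *β* = 0.1, and power = 0.9, 68 subjects are required in each group", "with a total of 136 subjects needed for the study". The section then adds: "Estimating a 20% dropout rate, a minimum recruitment of 160 subjects is required". It gives no superiority margin and no adjustment for a rank test.

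Statistical methods for primary and secondary outcomes {20a} describes the analysis: a t test, with Satterthwaite's correction if the variances differ, or the Wilcoxon rank-sum test if the data are not normal. On sidedness it says "The hypothesis test uses a two-sided test and gives the test statistics", and it counts p values of 0.05 or below as significant. Trial design {8} sets 1:1 allocation.

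**The concern.** The two sections use the same nominal level, 0.05, but attach it to different tests. A one-sided test at 0.05 has the critical value of a two-sided test at 0.10, so it needs fewer patients for the same power. If the trial really had been sized on that basis and then analysed two-sided at 0.05, one would expect a shortfall in power.

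The section also gives every input needed to recompute the number, and 68 does not come out. The evaluable number per group is the figure on which the power statement and the recruitment target rest. As printed, a reader cannot tell which calculation produced it.

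**Working it through.** **Inputs.** From Sample size {14}: difference 8 h; SDs 12.28 and 14.57; alpha 0.05; power 0.9; dropout 20%; recruitment 160. From Trial design {8}: 1:1 allocation.

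**Formula (normal approximation), per group:** n = (z_alpha + z_beta)² × (SD1² + SD2²) / difference².

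- SD1² + SD2² = 12.28² + 14.57² = 150.80 + 212.28 = 363.08
- 363.08 / 8² = 363.08 / 64 = 5.673

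**Attempt to reproduce 68 as described (one-sided 0.05, power 0.9):** (1.645 + 1.282)² × 5.673 = 48.6, so 49 per group. With the noncentral t distribution and Satterthwaite degrees of freedom it is 50. The stated 68 is 36% above 50 (68/50 = 1.36).

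**With the test that the analysis section prescribes (two-sided 0.05, power 0.9):** (1.960 + 1.282)² × 5.673 = 59.6, so 60 per group, or 61 with the t distribution. The stated 68 is 11% above 61 (68/61 = 1.11).

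Neither gap is a matter of rounding or of a t correction.

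**Power for 8 h with the stated SDs (t distribution, Satterthwaite df):**

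| Per group | One-sided 0.05 | Two-sided 0.05 |
|---|---|---|
| 64 (160 less 20%, halved) | 95.5% | 91.5% |
| 68 | 96.4% | 93.0% |
| 80 | 98.2% | 96.2% |

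**Routes that come near 68.** Each needs an input that the article does not state:

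- SD 14.57 in both arms, two-sided: 2 × 14.57² / 64 × (1.960 + 1.282)² = 69.7. This discards the stated 12.28.
- Two-sided with a rank-test efficiency of 0.864: 59.6 / 0.864 = 69.0. With the simple average of the two SDs, 13.425, it is 68.5.
- One-sided 0.05 with a superiority margin of about 1.2 h: 68.

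The value 0.864 is the standard lower bound for the efficiency of the Wilcoxon test relative to the t test. It is an assumption here, not a figure from the article. With the usual value for normal data, 0.955, the two-sided figure is 61 / 0.955 = 63.9, so 64.

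**Dropout.** For a 20% loss, recruitment is N / (1 − 0.2).

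- 136 / 0.8 = 170. Multiplying by 1.2 instead gives 164. Neither is 160.
- 160 covers 136 only up to a loss of 1 − 136/160 = 15%.
- 122 (2 × 61) / 0.8 = 152.5, so 153. Here 160 is enough.

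**The case against.** The strongest reply is that nothing practical turns on this. The only section that governs the analysis is explicit that the test is two-sided, and 68 exceeds the requirement under both readings. Both points stand, and they rule out two stronger conclusions that a reader might draw.

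- A reader might infer that a result with a two-sided p value between 0.05 and 0.10 could be called positive, or that the favourable-direction error rate rises from 2.5% to 5%. The article does not support this. The one-sided wording describes only how the number was computed; no one-sided analysis is planned, and under {20a} such a result is not significant.
- A reader might infer that the trial is underpowered for its two-sided test. On its own assumptions it is not: power stays above 90% even at 64 per group.

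It can also be said that the article condenses a fuller protocol and may have dropped a software setting, so that 68 could be correct and only the word for one-sided wrong. That is possible, and it is a reason to trace the calculation before replacing the number. It does not remove the point. The section presents a complete set of inputs with a result that they do not give, and the near matches that use a two-sided test contradict the one-sided description as well.

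**Conclusion.** The point holds as an inconsistency and an irreproducible figure of moderate weight. The sample size section and the analysis section name different tests at 0.05. The stated 68 per group should be 49 to 50 under the former or 60 to 61 under the latter, so it is too high by about 18 or 7 patients per group against the t-based figures (68 − 50; 68 − 61). The error is in the safe direction, and the planned two-sided analysis keeps its 5% level.

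This rests on the article's own difference and SDs, on equal allocation, and on the t test as the primary comparison. It does not establish how 68 was obtained.

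**What to change.** 1. In Sample size {14}, delete the one-sided description and state two-sided alpha 0.05, to match {20a}.
2. Check the PASS calculation as it was run. If 68 rests on a further input (a margin, a larger SD or a rank-test correction), state that input and confirm that it is compatible with a two-sided test. If there is none, restate the requirement as 61 evaluable per group, 122 in total, for a t test with 90% power.
3. Give the dropout arithmetic with the chosen number. With 122, 153 recruits are needed at 20% loss and 160 suffices. If 68 per group is kept, 20% loss would need 170, so at 160 the tolerated loss must be restated as 15%.

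The cost is one rewritten paragraph and a look at the software output. Neither enrolment nor the planned analysis changes.

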### Trial design {8}

The study is a single-center, prospective, parallel, randomized controlled clinical trial. Subjects who fulfill inclusion criteria and signed the informed consent form will be randomly assigned to either the acupuncture group (AG) or control group (CG) in a 1:1 ratio. Assessments are made prior to treatments and on the 4th day and 1 month after the treatments (Fig. 1).

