### Recruitment {15}

One hundred sixty patients are recruited from the Colorectal Surgical In-patient Department of CICMAS through publication and distribution of posters and leaflets containing information of the study.

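### Sample size: 136 evaluable patients, 20% dropout and a minimum of 160 recruits do not agree; 160 covers 15% loss, and 20% loss would need 170

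*Protocol article*

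**What the plan says.** Everything needed is in the protocol article, mostly in Sample size {14}.

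- Evaluable number: "68 subjects are required in each group, with a total of 136 subjects needed for the study".
- Loss allowance and recruitment target: "Estimating a 20% dropout rate, a minimum recruitment of 160 subjects is required".
- Design inputs: "a mean decrease of 8 h in time of first flatus", with standard deviations "between the study group and control group to be 12.28 and 14.57, respectively", and "Using *α* = 0.05, *β* = 0.1, and power = 0.9".

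The total of 160 is the working target throughout. Recruitment {15} repeats it ("One hundred sixty patients are recruited from the Colorectal Surgical In-patient Department"), and the Abstract gives it as 80 per group, in line with Trial design {8}, which assigns patients to "either the acupuncture group (AG) or control group (CG) in a 1:1 ratio". No section gives another loss rate or another evaluable number.

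One further rule matters. Criteria for discontinuing or modifying allocated interventions {11b} lets a patient with too much missing data be replaced. It sets no threshold or number of replacements, and it does not change the 160.

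**The concern.** The section presents 160 as the result of adding a 20% allowance to 136, and calls it a minimum. A total meant to protect 136 evaluable patients against 20% loss has to be large enough that 80% of it is at least 136, and 160 is not.

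The matter at stake is which figure governs. If the trial loses exactly the share it planned for, a reader comparing the final count with the stated requirement will see a shortfall of the plan's own making. The explanation would then have to be given after the results are known. Recruitment was still open when the article was written (Trial status), so the figures could be reconciled in advance.

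**Working it through.** **Inputs.** From Sample size {14}: 68 per group, 136 in total; loss 20%; recruitment 160; difference 8 h; SDs 12.28 and 14.57; α = 0.05. From Trial design {8}: 1:1 allocation. From Statistical methods for primary and secondary outcomes {20a}: a two-sided test, by t test or, if the data are not normal, Wilcoxon rank-sum.

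**Step 1: try to reproduce 160 from 136 and 20%.**

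- Evaluable total: 2 × 68 = 136, as stated.
- Correct inflation, N/(1 − d): 136/(1 − 0.20) = 170, or 85 per group. This is 10 more than 160.
- Common shortcut, N × (1 + d): 136 × 1.2 = 163.2, so 164. This is closer, but still above 160.

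Neither gives 160, and rounding does not explain it, because a minimum is rounded up.

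**Step 2: find the loss rate that 160 does match.**

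1 − 136/160 = 1 − 0.85 = 15%. Conversely, 136/0.85 = 160 exactly.

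**Step 3: what 160 leaves at 20% loss.**

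160 × 0.80 = 128, or 64 per group. That is 136 − 128 = 8 fewer than stated (4 per group), if every loss is a loss of the primary outcome and none is replaced.

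**Step 4: does this bring power below the planned 90%?**

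- Variance sum: 12.28² + 14.57² = 150.80 + 212.28 = 363.08.
- Standard error at 64 per group: √(363.08/64) = 2.382 h.
- Standardised difference: 8/2.382 = 3.359.
- Two-sided power, normal approximation: Φ(3.359 − 1.960) = Φ(1.399) = 91.9%.
- The same by noncentral t with Welch degrees of freedom: 91.5%.
- Wilcoxon on normal data, taking the usual relative efficiency of 0.955: 64 × 0.955 = 61.1 effective per group, about 90.2%.
- One-sided, as the sizing paragraph has it: 95.5% by noncentral t.

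For comparison, the stated 68 per group gives 93.0% two-sided by noncentral t, so going from 68 to 64 costs about 1.5 percentage points.

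**Step 5: how far the reassurance depends on the SDs.**

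If both groups had SD 14.57, 64 per group would give 86.9% two-sided power by t test. The result in step 4 therefore holds for the stated pair of SDs and should be reported with that condition.

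**The case against.** Four things can be said for the plan.

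1. *Losses may be replaced.* Section {11b} allows it, so 128 need not be the final count. This stands against any claim that the trial will end short. It does not rescue the arithmetic: the rule carries no number, and the sample-size section presents 160 as the product of the 20% allowance, with no mention of replacement.

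2. *Not every dropout loses the primary outcome.* First flatus is an early postoperative event, data gathered before withdrawal are kept under {11b}, and the primary analysis is by intention to treat under {20c}. A patient lost before the one-month visit may already have supplied it. This also stands, and it makes 128 a cautious count. But the sponsor chose to inflate for dropout, and the inflation as printed is wrong.

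3. *The gap is small.* Against the shortcut it is about 2% (160 versus 163.2); against the correct formula it is about 6% (160 versus 170). Either way the stated minimum is too low for its own premises.

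4. *Power survives.* True on the stated inputs, and it determines how the point should be rated.

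A reader might infer something stronger: that the trial is underpowered, or must recruit 170. The documents do not support that. On the stated difference and SDs, 64 per group keeps at least 90% two-sided power, and replacement or early capture of the outcome could leave more than 64. A target of 170 follows only if the sponsor insists on both 136 and 20%.

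**Conclusion.** The inconsistency is real, and nothing elsewhere in the article resolves it. With 136 evaluable patients and 20% loss the recruitment figure should read 170; with 136 and 160 the loss rate should read 15%; with 160 and 20% the evaluable number should read 128. The size of the error is 10 recruits, or 8 evaluable patients.

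It is an error in the stated figures. Power at 64 per group is about 91% by t test and about 90% by Wilcoxon on normal data. This assumes an 8 h difference, SDs of 12.28 and 14.57, a two-sided 0.05 level and no replacement of losses. It should be corrected, but it gives no reason to enlarge the trial.

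Two neighbouring questions are separate and are not settled here: whether 68 per group is the right base for the stated inputs, and the conflict between sizing by a one-sided test ("Using a unilateral test of superiority, PASS.11 software is used to compute sample size") and the two-sided analysis in {20a}.

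**What to change.** Keep 160 and rewrite the last sentence of Sample size {14} so that the three figures agree. For example: *Recruiting 160 patients (80 per group) allows for 15% loss from 136. At 20% loss, 128 patients (64 per group) would remain, giving about 91% two-sided power for a difference of 8 h by t test, or about 90% by Wilcoxon test on normal data, assuming SDs of 12.28 and 14.57.*

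The sponsor should also say which loss rate was intended, since the documents give no ground for preferring 15% to 20%, and whether replacements under {11b} fall inside or outside the 160.

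The cost is one sentence, plus a clause on replacement. The Abstract and Recruitment {15} can stand, and no additional patients are required.
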